## Abstract

**Introduction:**

Paediatric acquired brain injury is a leading cause of mortality in children in the UK. Improved treatment during the acute phase has led to increased survival rates, although with life-long morbidity in terms of social and emotional functioning. This is the protocol for a feasibility randomised controlled trial with an embedded qualitative study and feasibility economic evaluation. If feasible, a later definitive trial will test the effectiveness and cost-effectiveness of an online intervention to enhance problem solving ability versus treatment as usual.

**Methods and analysis:**

Twenty-five adolescents and their families identified by primary or secondary care clinicians at participating UK National Health Service Trusts will be recruited and individually randomised in a 1:1 ratio to receive the online intervention or treatment as usual. Participants will be followed up by online questionnaires 17 weeks after randomisation to capture acceptability of the study and intervention and resource use data. Qualitative interviews will capture participants’ and clinicians’ experiences of the study.

**Ethics and dissemination:**

This study has been granted ethical approval by the South West-Exeter Research Ethics Committee (ref 17/SW/0083). Results will be disseminated via peer-reviewed publications and will inform the design of a larger trial.

**Trial registration number:**

ISRCTN10906069

Strengths and limitations of this studyThis is the first study to test an online problem-solving tool for adolescents who have survived a brain injury in the UK.The study explores the feasibility of recruitment strategies, data collection and economic evaluation to inform the design of a larger randomised controlled trial.The effect of the online intervention on executive functioning is not assessed.This study is conducted online, with minimal telephone support and no face-to-face contact.This feasibility study was conducted over a short time period thus limiting the opportunity for a long-term follow-up. The definitive trial would include a follow-up period of at least 6 months.

## Introduction

In 2012, paediatric acquired brain injury (pABI) was identified as one of the leading causes of death in children aged 5 to 19 years^1^. In the UK, 280 children per 100 000 require at least 24 hours hospitalisation for traumatic brain injury (TBI) each year.^2^ When considering other aetiologies such as brain tumours, stroke and infection, there are even greater numbers of children surviving pABI.^3^The long-term, even life-long, effects on social functioning, cognition, emotions and behaviour mean that pABI is a leading cause of disability.^4 5^

Despite these on-going difficulties, children with pABI do not automatically receive specialist education, often returning to mainstream schools with little or no additional support. Furthermore, although specialist tertiary National Health Service (NHS) services do exist in the UK, there are limited outreach support or community services for ongoing and emerging difficulties.^6^ Families report struggling to access appropriate treatments despite their child developing significant and complex needs. Families also report significant distress and burden when caring for a child who has survived pABI, leading to an increased risk of mental health difficulties in parents and siblings, and a breakdown in parental relationships.^7^ Without appropriate neuropsychological interventions, pABI can lead to increased risk of substance misuse,^8^ mental health difficulties,^9^ unemployment and criminal behaviour in adulthood.^10^ Thus, the long-term costs of pABI to the individual, his/her family and society as a whole can be substantial.^11^

Executive function (EF) difficulties (higher-order cognitive processes that govern goal-directed action and adaptive responses to novel or complex situations) are common following pABI.^12^ These difficulties can present later in childhood (particularly in early adolescence), sometimes many years after the initial brain injury. EF difficulties can have far reaching effects, including problems with academic achievement,^13^ social communication,^14^ emotion and behaviour regulation^15^ and peer relationships.^16^ Indeed, families caring for children with pABI often report that EF difficulties significantly contribute to their increased levels of stress.^17^ Effective interventions targeting child EF and family burden are likely to have significant patient benefit especially as developmental studies show that poor family function can also negatively impact on the child’s development of EF abilities.^18^

Despite the clear negative impact of EF difficulties following pABI, there is currently a paucity of research examining the effectiveness of interventions to improve function.^19^ In an attempt to address this gap, Wade and colleagues developed an online web-based problem-solving, communication and self-regulation intervention for adolescents (12 to 17 years) who have survived a TBI, and their families (Teen Online Problem-Solving, TOPS).^20^ The development of online family problem-solving treatment for paediatric TBI was predicated on evidence of the reciprocity between child recovery and parental psychological well-being and informed by input from survivors of TBI and their families. Problem-solving therapy provides a systematic approach for coping more effectively with life’s challenges by creating a positive mindset and developing, implementing and evaluating solutions to problems.^21^ Online family problem-solving treatment simplifies the ABCDEs of problem-solving: defining the Aim, Brainstorming, Choosing the best strategy to implement, Doing it (creating a concrete, step-by-step plan) and Evaluating whether it worked. Given the focus on the family rather than the individual, TOPS also focuses on communication skills and collaborative problem-solving. For adolescents with executive function and problem-solving deficits following TBI, the steps of problem-solving also provide an executive function heuristic.^22^ Additionally, the programme teaches stress management and metacognitive strategies such as stopping to think before acting and self-monitoring that can serve to promote self-regulation. Similar to the face-to-face, multifamily Brain Injury Family Intervention,^23^ online modules provide didactic information regarding the cognitive and behavioural consequences of TBI, training in problem-solving, communication and self-awareness/regulation and exercises to reinforce understanding. After completing the online modules on their own, families meet with a trained therapist to implement to the problem-solving process around an Aim (goal) that they have identified. Thus, the online problem-solving programme was grounded in the scientific literature, tailored to address the unique neurobehavioral and family consequences of TBI and refined through stakeholder input.^20^ Problem-solving therapy has also been trialled as a telephone-based intervention for adults with mild TBI and with families of adults with more significant brain injury,^24^ suggesting its potential utility across age groups and modes of delivery.^25^

Research to date has been undertaken in the USA, and has focused on children and adolescents who have survived a TBI and their families.^20 26–31^ These studies have demonstrated improvements in EF, child behaviour, parental depression and family-child conflict when comparing TOPS with an internet-resource comparison control. Families have reported finding the online delivery of the intervention helpful, making the intervention easy to access at a time that is convenient for them. This is an important consideration when providing interventions for children with pABI in the UK and their families, because brain injury services in the UK often cover a large geographical region (many accepting national referrals), and families often have multiple commitments when caring for these teenagers with complex needs.

Despite this emerging evidence base, it is not yet known whether the gains described can also be demonstrated in adolescents with non-traumatic brain injuries (eg, brain tumour, stroke), when the intervention is delivered remotely (ie, no initial home visit to set up the intervention thus keeping delivery costs to a minimum), and if the intervention is cost-effective relative to treatment as usual (TAU).

A British version of the TOPS programme, (TOPS-UK) has been developed. The didactic material is presented with British English spelling and narration, UK-based information including scenarios, video clips and resource links. TOPS-UK has been further modified to include examples of those with paediatric acquired brain injury as well as traumatic brain injury.

The potential of TOPS-UK to have a positive effect on the lives of thousands of adolescents with pABI needs testing in a rigorous multicentre, randomised controlled trial (RCT) in the UK, allowing a definitive test of its clinical and cost-effectiveness. This feasibility study is designed to determine if a large RCT is feasible, with the ultimate aim of the research being to provide an evidence base for effective neuropsychological interventions to be recommended by the Department of Health guidelines (eg, NICE) for survivors of pABI.

A two-arm randomised controlled feasibility phase II study will be conducted.^32^ The aim is to assess whether a larger, fully powered, definitive RCT and cost-effectiveness analysis can be successfully planned and delivered. In order to gain as much information as possible to inform a fully powered RCT, additional objectives are considered in this feasibility trial, including accessing information related to treatment set-up, delivery costs and resource use (table 1).

**Table 1 T1:** Study objectives

Number	Study objectives
1	Are clinicians able and willing to identify participants (eg, has time and access to database, medical records or clinic lists to identify potentially eligible patients)?
2	Are the online screening, consent and randomisation process feasible?
3	How many participants at each site are initially eligible, approached and consented, have completed screening and baseline questionnaires, been randomised (with a recruitment target of at least five participants per site), completed treatment and completed outcome assessments?
4	Do adolescents and parents find the intervention and outcome measures acceptable?
5	What are parents’ and adolescents’ experiences of study participation?
6	Is it possible to calculate means and SD for a full RCT for the potential primary outcome measure?
7	What resources will be required to run a main trial?
8	Do some sites need additional support to be able to recruit to target in a future trial?
9	Do the trial and economic evaluation methods and procedures yield the information required?
10	How willing are participants to be randomised and complete outcome measures?
11	How well do participants adhere to the intervention (number of sessions completed)?
12	How many complete and analysable data sets are yielded, and what is the level of missing data?
13	How many participants are lost to follow-up?
14	What is the coach’s experience of supporting intervention delivery?
15	What are adolescent and parent experiences of TAU? (TAU arm)

RCT, randomised controlled trial; TAU, treatment as usual.

## Methods and analysis

This is a randomised, controlled, multicentre feasibility study in young patients with pABI aged 12 to 18 years. Twenty-five participants will be randomised (minimised by site and type of brain injury) in a 1:1 ratio to receive TAU or treatment as usual plus Teen Online Problem-Solving (TAU + TOPS UK). Treatment allocation will not be blinded. The protocol (V.4.1, 30 August 2018) is registered on Current Controlled Trials ISRCTN10906069 and follows Standard Protocol Items: Recommendations for Interventional Trial guidelines.^33^

### Setting

Two settings will be utilised to examine feasibility outcomes associated with recruitment of adolescents known to have had a pABI:Direct referral by clinicians of adolescents who are under the outpatient care (usually neurology, neuropsychology or paediatric) of five participating NHS Trusts in England. Screening logs will be maintained at all sites to record the number of patients screened and enrolled in the study. These sites were selected to be representative of the range of types of services which might be included in a future trial, with TAU ranging from no provision through to services providing multidisciplinary outpatient care over the long-term.Recruitment from Participant Identification Centres (PICs) in primary or secondary care, or charitable organisations. Potential participants will respond directly to study promotion including leaflets/posters/participant information sheets distributed by parent-led groups, charities or support groups.

Study participation will be supported by research nurses at each participating NHS Trust. For participants directly referred to the study, nurses will make the first approach to the family. For those identified through PICs, families will be asked to contact the research nurse whose details are provided on the patient information sheet (PIS). The research nurse will support all families during the online consent and will be a point of contact for all participants during the study. The research nurse or other research team member will support baseline and follow-up measure completion. The intervention will be provided through online materials and video conference links with a coach trained in the TOPS-UK intervention. The coach will also receive weekly supervision from a qualified clinical psychologist on the research team to ensure treatment fidelity. The single study coach will be centrally based at the lead site.

### Participant inclusion criteria

To be included in the study, participants will be aged 12 to 18 years at the time of recruitment and have survived a pABI. Diagnosis of pABI includes: moderate-to-severe TBI (Glasgow Coma Scale score <12 and/or post-traumatic amnesia >24 hours and/or loss of consciousness >30 min), stroke, brain tumour, central nervous system infection (fungal, bacterial protozoal or viral origin including encephalitis, meningitis, brain abscess, tuberous sclerosis, acute disseminated encephalomyelitis and Guillain-Barre syndrome). Participants must be medically stable (having reached a plateau in recovery following the index injury or illness). They must also have access to the internet, and have EF difficulties in the opinion of the local Principal Investigator (PI). The local PI is not required to undertake any EF assessment for the purposes of the study, but will use their clinical judgement, and infer from any assessments that they have undertaken, whether a participant is likely to be experiencing EF difficulties in their everyday lives. At least one parent or guardian living with the adolescent must be available for the family to participate. Adolescents with a comorbid diagnosis of attention deficit hyperactivity disorder, autistic spectrum disorder or specific learning difficulties (eg, reading difficulties including dyslexia) will be eligible to be recruited.

### Participant exclusion criteria

Participants will be excluded from the study for the following reasons: insufficient English language, capacity or willingness for the parent/adolescent to consent/assent to the study; pre-injury or comorbid conditions such as sensory impairments and global developmental delay, known to impair engagement with the computer and treatment materials; or non-accidental brain injury.

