### Participant recruitment

The trial complies with the Declaration of Helsinki and Good Clinical Practice (GCP) guidelines. GCP compliance ensures that the rights, safety and well-being of research participants are protected and that research data are reliable. At sites, the local PI, research nurse or other member of the research team in conjunction with the clinical team will identify potential eligible participants, usually from current outpatient clinic lists or review of medical records. An anonymised log of all participants screened with reasons for exclusion will be kept at site. Information sheets for both adolescents and their parents/guardians will be provided to potentially eligible families. The relevant PIS will be given in person to families attending an outpatient clinic, or sent by post with a cover letter from the recruiting clinician. All families will be provided with contact details and informed that a member of the research team will contact them by telephone at least 24 hours after receipt of the information to discuss the study.

During this telephone call, the parent and adolescent will be given the opportunity to ask questions about the study and to confirm whether they are interested in participating. If interested, eligibility criteria will be checked with the parent to confirm suitability for the study and ascertain which parent will participate in the intervention and complete parent-rated outcomes. A summary of what to expect from the online screening and consent process will also be provided.

The process of explaining the study and determining eligibility of potential participants will be undertaken by an appropriately trained member of the research team as delegated by the PI, depending on local arrangements. All staff undertaking this process for this study must have completed GCP training provided by a responsible organisation (eg, University, NHS Trust) and must be authorised by the PI to explain the study and assess eligibility, on the site’s study delegation log.

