#### Web-based consent process

The research nurse will enter on the study website brief details of those families who wish to participate in the study and who satisfy the initial inclusion/exclusion criteria. This will trigger an email to the adolescent, containing a link to the age-appropriate assent or consent form within the website, which the adolescent should complete.

Following completion of the adolescent assent/consent form, a separate email will be sent to the nominated parent participant containing a link to the parental consent form. Parents of adolescents aged 12 to 15 years will be asked to consent on behalf of their adolescent in addition to giving consent for their own participation. Two reminder emails will be sent from CTU followed by a ‘last chance’ email, all with reminders of the study link. If the family has not completed the consent process after 2 weeks, the local research team will be notified and will contact the family to ask if they still wish to participate in the study.

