#### Assessment of trial feasibility

The primary feasibility outcomes of this study include: (i) number of participants at each stage of the study, at each site, with stages including: identified as potentially eligible, approached, consented to study, completed screening and baseline, randomised (with at least five participants being recruited at each site), completed treatment and completed outcome assessments; (ii) any difficulties experienced at sites that may affect their ability to recruit in future will be identified and reviewed; (iii) evaluation of appropriateness of the trial and economic evaluation methods and procedures; (iv) assessment of participants’ willingness to be randomised to treatment allocation; (v) adherence to treatment assessed as number of sessions completed, a session will be recorded as complete if the participant has been through every page, reached the end and completed the coach web-linked session related to that material (with a target of participants completing at least five sessions) and (vi) attrition (with a target of at least 80% of participants completing follow-up assessments).

We will report the proportion of screened families who are found to be eligible, the proportion of eligible families who are recruited and randomised to their allocation and the proportion of randomised participants who provide outcome data at follow-up, with 95% CIs. Our sample size of 25 participants will allow us to estimate loss to follow-up (anticipated to be 20%) with a 95% CI of +/-13 percentage points. The further outcome is evaluation of the SD of the BRIEF-2 (parent) score for this patient population. This is the proposed primary outcome for the main trial and required for calculation of the sample size.^36^

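### Unwillingness to consent is an exclusion criterion, so read literally decliners leave the eligible denominator and the recruited/eligible proportion no longer measures uptake

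*Protocol article*

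**What the plan says.** All references are to the protocol article.

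- *Participant exclusion criteria*: the reasons for exclusion include "insufficient English language, capacity or willingness for the parent/adolescent to consent/assent to the study". Willingness stands in the same list as language, capacity, comorbidity and non-accidental injury.
- *Participant recruitment*: site staff "will identify potential eligible participants, usually from current outpatient clinic lists or review of medical records". After information has been given, the family is telephoned. "If interested, eligibility criteria will be checked with the parent to confirm suitability for the study". For the log, "An anonymised log of all participants screened with reasons for exclusion will be kept at site".
- *Web-based consent process*: the nurse enters on the website "brief details of those families who wish to participate in the study and who satisfy the initial inclusion/exclusion criteria". Losses can still follow: "If the family has not completed the consent process after 2 weeks, the local research team will be notified".
- *Assessment of trial feasibility*: the reported results include "the proportion of screened families who are found to be eligible, the proportion of eligible families who are recruited and randomised to their allocation", with 95% CIs. The stage counts at each site are a primary feasibility outcome and include "identified as potentially eligible, approached, consented to study, completed screening and baseline, randomised". Item (iv) of the same list is willingness to be randomised.
- *Table 1*: objective 3 lists an initial eligibility stage ahead of approach and consent. Objective 10 asks how willing participants are to be randomised and to complete outcome measures.
- *Sample size calculation*: 20 screened at each of five sites, 100 in total, with 25 recruited. No eligibility rate or consent rate is given.

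**The concern.** The two proportions answer different planning questions. Eligible/screened tells the definitive trial whether sites see enough suitable patients. Recruited/eligible tells it whether suitable families accept the trial. To separate these, a family that is suitable but declines has to count as eligible.

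The exclusion criterion does the opposite: a decliner is an excluded family. The order of the telephone call points the same way, because a family that says no on the call does not reach the confirmatory check. Followed as written, refusal moves from the second proportion into the first, and a problem of acceptance would look like a shortage of suitable patients. Willingness would also be both something the study measures and a condition for entering the denominator in which uptake is measured. If some sites apply the criterion literally and others follow the sequence in objective 3, the proportions would not be comparable between sites.

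**Working it through.** **Planned figures.** 5 sites × 20 = 100 screened and 5 sites × 5 = 25 recruited. Both reproduce the stated totals. Recruited/screened = 25/100 = 25%.

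**Notation.** S = 100 screened and R = 25 randomised (from the article). D = clinically eligible families who decline before the eligibility check. L = families who pass the check but are lost before randomisation, for example through uncompleted consent or baseline measures. E = R + L + D = all clinically eligible families. The article gives neither E nor L; I assume E = 40 to 80 and L = 0 to 10.

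**Two definitions of eligible.**

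- (a) Decliners kept in: eligible/screened = E/S; recruited/eligible = R/E.
- (b) Decliners removed, as the exclusion criterion literally requires: eligible/screened = (R + L)/S; recruited/eligible = R/(R + L).

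Under (b), recruited/eligible does not contain D, so it takes the same value however many families refuse. It exceeds (a) by the factor E/(R + L) = 1 + D/(R + L), which is above 1 whenever anyone declines.

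**Results, with exact (Clopper-Pearson) 95% CIs for recruited/eligible.**

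| Definition | Assumption | Eligible/screened | Recruited/eligible |
|---|---|---|---|
| (a) | E = 40 | 40% | 25/40 = 62.5% (45.8–77.3) |
| (a) | E = 50 | 50% | 25/50 = 50.0% (35.5–64.5) |
| (a) | E = 60 | 60% | 25/60 = 41.7% (29.1–55.1) |
| (a) | E = 80 | 80% | 25/80 = 31.3% (21.3–42.6) |
| (b) | L = 0 | 25% | 25/25 = 100% (86.3–100) |
| (b) | L = 3 | 28% | 25/28 = 89.3% (71.8–97.7) |
| (b) | L = 5 | 30% | 25/30 = 83.3% (65.3–94.4) |
| (b) | L = 10 | 35% | 25/35 = 71.4% (53.7–85.4) |

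**Check.** In every row the two proportions multiply to 25%, for example 0.60 × 0.417 and 0.30 × 0.833. The definition only changes how the same overall yield is divided between eligibility and uptake.

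**Size of the shift.** It is smallest at E = 40, L = 10 (D = 5): 62.5% becomes 71.4%, a factor of 40/35 = 1.14, with overlapping intervals. It is largest at E = 80, L = 0 (D = 55): 31.3% becomes 100%, a factor of 80/25 = 3.2. A middle case, E = 60 and L = 5 (D = 30), goes from 41.7% to 83.3%, a factor of 60/30 = 2.

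**The case against.** Four arguments stand against the point.

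1. *Eligibility is judged before interest is asked.* This is correct. Records are reviewed before approach, executive function difficulty rests on the local investigator's judgement, and objective 3 puts initial eligibility first. A reader might infer that eligibility is assessed only in interested families; that is true of the confirmatory check with the parent, not of all screening. Objective 3 therefore offers a sensible denominator that keeps decliners in. But the feasibility section does not adopt it, and the exclusion criterion contradicts it.

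2. *The information is collected anyway.* This is largely true for direct referrals. Exclusion reasons are logged, and potentially eligible, approached and consented families are counted at each site, so uptake could be approximated. It is less true for families reached through Participant Identification Centres, who contact the nurse themselves; those who decide against it are never observed. The possibility of rebuilding uptake does not correct the proportion that the article says will be reported.

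3. *No decision depends on it.* The stated numerical targets are five recruits per site, five sessions and 80% follow-up; none uses recruited/eligible. A reader might infer that the sponsor will mistake refusal for ineligibility and change the wrong thing. That would require overlooking the log and the counts, and the documents do not show that it would happen.

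4. *Definitions may sit in the full protocol.* Denominator detail often does, and its mere absence would be no finding. Here, however, the article states a rule that removes decliners and another stage order that keeps them.

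**Conclusion.** The point holds as a conflict between stated rules with a known direction of bias. If the exclusion criterion is applied literally, eligible/screened is too low and recruited/eligible too high as a measure of uptake. For 100 screened and 25 randomised, recruited/eligible is 71–100% instead of 31–63%, and eligible/screened is 25–35% instead of 40–80%. These ranges rest on the assumed 40 to 80 clinically eligible families and 0 to 10 later losses. The direction does not depend on those values, provided at least one clinically eligible family declines.

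A reader might infer that recruited/eligible will come out at about 100%. The documents do not support that: it needs no loss at all between the eligibility check and randomisation, or late non-completers also being classed as unwilling. Nor do they show that decliners will certainly be counted as ineligible, since objective 3 supports the other reading. The matter deserves correction because the proportions are headline results of a feasibility study. It does not threaten participants or the main feasibility targets.

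**What to change.** - In *Participant exclusion criteria*, delete willingness and leave language and capacity. Consent is already a separate step.
- On the screening log, record declined as an outcome of its own, distinct from ineligible.
- In *Assessment of trial feasibility*, define the denominator of the recruitment proportion as families judged potentially eligible on record review or investigator assessment and approached, minus those found ineligible on clinical criteria. Decliners stay in.
- Report next to it the proportion among families whose eligibility was confirmed, labelled as such.
- Report the Participant Identification Centre route separately and state that its refusers are not observed.

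The cost is one word removed, one log category and a few sentences. The reported recruitment proportion will look less favourable. For some decliners eligibility will stay unconfirmed, because internet access or an available parent usually has to be asked of the family; reporting both proportions shows how much this matters.
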